## Results

### Data Collection

All data will be anonymous, and files will be secured with a password. In objective 1, the results of the GRS and Subcuticular Suture Checklist for all participants will be collected through GEN. In objective 2, the expert evaluating the videos will compile the data in one file that will not be published on GEN. Responses from the acceptance survey will be collected using Qualtrics XM.

### Statistical Analysis Plan

First, we will perform descriptive statistical analyses to assess the distributions of the variables of interest and determine the appropriate tests to use as well as the need for a potential transformation. Continuous variables with an asymmetric distribution will be described using median (IQR). Categorical variables will be described with proportions. The remaining variables will be described with mean (SD).

In the following paragraphs, we describe our statistical plan assuming a Gaussian distribution.

Objective 1: We will perform balanced one-way ANOVA to compare mean GRS and Subcuticular Suture Checklist scores among all four groups. First, distinct analyses of the pretest and the posttest scores will be performed. Then, the mean difference between the pretest and the posttest scores will be compared using paired *t* tests if the difference between paired values is consistent.

Objective 2: We will perform balanced one-way ANOVA to compare the performance of students in executing a running subcuticular suture as assessed by the GRS and the Subcuticular Suture Checklist.

Objective 3: We will perform descriptive statistical analyses and correlate the study groups with the Likert scales using the Kruskal-Wallis equality-of-population rank test.

Analysis will be performed in RStudio version 1.2.5033 (RStudio Team) [36] and GraphPad Prism version 8.0.0 for Mac OS X (GraphPad Software) [37]. For each analysis, confidence intervals will be calculated for a 95% confidence level. Statistical hypothesis testing will be performed with an alpha threshold of .05.

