#### Errors

Each video with errors will include 1 to 3 errors from the list detailed below:

The needle holder is held with the thumb and index finger instead of the thumb and fourth finger.The thumb is entirely inserted in the ring of the needle holder.The needle is not held at two-thirds in the jaw of the needle holder.Suturing is performed at an incorrect depth.Excessive force is used with the forceps.The needle is not inserted at a 90º angle.Sutures are at inappropriate distances.Extra unnecessary steps are performed.The knot is not sufficiently tight.Supination and pronation are not properly performed.The thread is cut at an inappropriate length after tying the knot.The thread is cut without seeing the knot.

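### The primary test and any transformation are left to be chosen after the outcome distributions are inspected, with no criterion and no named fallback for objectives 1 and 2

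*Protocol article*

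**What the plan says.** All of the relevant text is in the protocol article, under Statistical Analysis Plan.

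- The first step is to look at the data in order to "assess the distributions of the variables of interest and determine the appropriate tests to use as well as the need for a potential transformation".
- What follows is conditional: "In the following paragraphs, we describe our statistical plan assuming a Gaussian distribution".
- Objective 1 (primary): "We will perform balanced one-way ANOVA to compare mean GRS and Subcuticular Suture Checklist scores among all four groups", separately for pretest and posttest. Paired t tests on the change are then run "if the difference between paired values is consistent".
- Objective 2 also uses one-way ANOVA on the two scales.
- Objective 3 (survey) has a rank test: the plan will "correlate the study groups with the Likert scales using the Kruskal-Wallis equality-of-population rank test".
- Alpha: "Statistical hypothesis testing will be performed with an alpha threshold of .05".

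The Sample Size section is built on the same one-way ANOVA model, using the GRS. The abstract reports that recruitment has not begun.

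**The concern.** This is a stated procedure, not a detail that a short article happens to omit. The outcome variables are to be examined, and the test and scale of analysis then follow from what is seen. A fuller analysis plan that fixed the test would contradict this sentence, so the sentence itself needs changing.

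Two things are at stake. First, the reported p value becomes one of several that could have been reported. Second, and more important for the reader of the results, the candidate analyses do not estimate the same thing. ANOVA compares mean scores, a log-scale analysis compares means of a transformed score, and Kruskal-Wallis compares ranks. The meaning of the effect and its confidence interval would be decided late, and could differ between the GRS and the checklist. The condition on the paired t tests adds a second open choice, because the plan does not say what makes paired differences *consistent*.

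**Working it through.** **1. Inputs from the article.** Four arms of 15 and alpha 0.05. The GRS in Table 1 has 8 items scored 1 to 5, so it runs from 8 to 40 per video. The checklist has 2 + 4 + 12 + 3 + 2 + 1 = 24 one-point steps. Groups 2 to 4 rate eight expert videos, six with errors ("Each video with errors will include 1 to 3 errors from the list detailed below"). The control arm rates eight correct videos.

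**2. The plan's own figure.** The stated 13 per group reproduces for a balanced four-group ANOVA if 0.8 is read as the between-group SD and 1.45 as the within-group SD. The article does not state that reading. It gives Cohen f = √(3/4 × 0.64 / 2.1025) = 0.478. The figure bears on this point only because it presupposes ANOVA.

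**3. Could the unwritten branch be needed?** Assume that each inserted error costs one checklist point. With an average of a errors per erroneous video, an accurate rater's mean over the eight videos is 24 − 6a/8:

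- a = 1: 23.25 (97% of maximum)
- a = 2: 22.5 (94%)
- a = 3: 21.75 (91%)

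The control arm's accurate score is 24. Bunching near the top of the checklist is therefore plausible. No such key can be derived for the GRS.

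**4. Error rate of a late choice.** Null trials, four arms of 15, 6,000 replicates per setting, Monte Carlo standard error about 0.3 percentage points. The score distributions are assumptions:

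- near-normal: mean 16, SD 1.45
- ceiling: 8 × 24 = 192 steps per student, with the probability of ticking a step drawn from Beta(9, 1), mean 0.90
- stronger ceiling: the same with Beta(6, 0.3), mean 0.95

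The log analysis uses log(25 − score). The distribution-driven rule applies Shapiro-Wilk to the within-arm residuals, then Kruskal-Wallis if p < 0.05 and ANOVA otherwise.

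| Rejections under the null | Near-normal | Mean 90% of maximum | Mean 95% of maximum |
|---|---|---|---|
| ANOVA | 5.0% | 4.4% | 4.0% |
| Log-ANOVA | 4.8% | 4.9% | 5.1% |
| Kruskal-Wallis | 4.4% | 4.7% | 4.8% |
| Distribution-driven rule | 5.1% | 5.1% | 4.8% |
| Smallest of the three p values | 6.1% | 6.6% | 7.5% |
| Shapiro-Wilk p < 0.05 | 5% | 98% | 100% |

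A separate run gave 7.9% for the smallest p value at the strongest ceiling. A set with normal, reflected gamma and reflected exponential scores gave 6.5% to 6.9%. Any single test fixed in advance rejects in about 5% or less, ANOVA included.

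**5. Which arms can a fixed raw-score test compare?** Under the assumption in step 3, the accurate checklist score in control exceeds that in groups 2 to 4 by 6a/8, that is 0.75 to 2.25 points, even if all arms learn equally. For a four-arm ANOVA the noncentrality is λ = 15 × (3/4) × gap² / SD². If all errors are detected and the SD is 1.5 (assumed), λ = 2.8 at a gap of 0.75 and 25.3 at 2.25, so the test rejects in 24% to 99%. At an SD of 3, λ = 0.7 to 6.3 and it rejects in 9% to 51%. A permutation test does not cure this, because the arms are rating different material.

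**The case against.** The strongest reply is that the text makes the choice depend on the distributions, not on the p values. The smallest-p row therefore does not model the plan as written. This stands: the row is a worst case, and the closer model stays near 5%. A reader might infer that the primary p value is materially invalid, but the documents do not support that.

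A second reply is that ANOVA is named as the default, that the sample size rests on it, and that it holds its level under skew. This also stands, and it makes the repair easy. It does not remove the defect, because the opening sentence makes that default open to revision.

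A reader might also infer that both scores will sit at the ceiling, so that an unwritten analysis is certain to be used. That goes too far. The checklist key assumes one lost point per error, and some listed errors, such as the thumb fully inserted in the ring, have no clear matching step. The key describes accurate ratings, whereas the raters are novices who may score lower. For the GRS nothing can be derived. Nor is the whole plan Gaussian-only: objective 3 has a rank test.

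Finally, normality thresholds and blinded distribution checks are commonly left to a full analysis plan. Their absence alone would be no finding. What remains is the affirmative statement that inspection of the data determines the test.

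**Conclusion.** The point holds in a limited form. For objectives 1 and 2 the article commits to choosing the test and any transformation after the outcome distributions are seen. It states no criterion and no fallback, and it adds an undefined condition on the paired t tests. The main cost is that the quantity estimated is not fixed in advance.

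The cost in false positives is small: about 6.5% per scale instead of 5% if the most favourable of three analyses were reported (6.1% to 7.9% over the distributions tried), and about 5% if the choice follows only the distributions. These figures rest on assumed score distributions and on that particular set of three tests. The conclusion does not depend on a ceiling effect.

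**What to change.** - Delete the sentence that lets the distributions determine the test and transformation, and delete the condition on the paired t tests.
- Fix one primary analysis on the original score scale before any outcome data are seen. One-way ANOVA is adequate at 15 per arm; a permutation p value is an acceptable alternative.
- For objective 1, apply it to groups 2 to 4, which the Objective 1 section already treats as the main groups and which rate the same videos. Do not present a raw-score comparison with the control arm as a test of learning. Objective 2 does not have this problem, because there an expert rates each student's own suture.
- Keep Kruskal-Wallis and transformed analyses as labelled sensitivity analyses, and do any distribution checks blind to arm.

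The cost is a few sentences while recruitment has not started. There are two small downsides. A fixed ANOVA may be slightly less efficient if scores are strongly skewed. Dropping the control arm from the primary test also lowers power: at f = 0.48, close to the value inferred in step 2 of the working, 15 per arm gives 86.8% with four arms and about 80% with three.

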### Participant Recruitment

All students in their first year of medical school will receive an email inviting them to participate in the study. If they agree, they will be required to complete a consent form and provide a mailing address (Qualtrics XM).

All students enrolled in this study will be asked to participate using a personal computer. Students will be advised that participation will require their availability for one to three hours on three consecutive days. They will be advised not to study, practice, or view any external videos pertaining to suturing skills for the duration of the study.

When the students agree to participate, they will receive an email with the GEN platform link.

Students' previous experience with suturing will be surveyed, as well as the context of this experience (eg, workshop, former profession).

Upon creation of a new user account on GEN, students will be automatically randomized to one of the four groups and will only have access to the platform set for their study group.

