#### Group 1: Control Group

On GEN, each student will individually view eight videos of an expert performing a running subcuticular suture correctly as a pretest. The Objective Structured Assessment of Technical Skills (OSATS) Global Rating Scale (GRS) (Table 1) and Subcuticular Suture Checklist (Textbox 1) will be made available beside each video, and students will be required to fill out these assessments for each video. For three days, students will have access to a distinct set of videos on GEN to learn running subcuticular sutures. Three days later, each student will perform a subcuticular suture on a suturing pad and record their first attempt. Then, students will undergo a posttest with the same eight videos shuffled in a different order. The order of the videos will be the same for all students.

The OSATS, developed by the University of Toronto, is an accurate and validated method of assessing surgical skills in an operating room setting [33,34]. It comprises a GRS (Table 1) in which certain skills are graded from 1 to 5 (ie, respect for tissue, time in motion, knowledge of instruments, instrument handling, suture skill, flow of operation, knowledge of procedures, and final product).

The checklist is a list of verifications specific to the technique of interest to ascertain whether every step of the procedure was executed (Textbox 1). The checklist was built and revised by a focus group led by the principal investigator, who is the director of the clerkship surgical rotation in the Faculty of Medicine of Université de Montréal. The focus group was composed of one medical student, one junior surgery resident, and one senior surgery resident.

**Table 1 table1:** Global Rating Scores of the Objective Structured Assessment of Technical Skills [8,33,34]. The students will be asked to rate the candidate’s performance on a scale of 1 to 5, and the total score will be summed.

Skill	Potential scores for observed outcomes				
	1-2		3		4-5
Respect for tissue	Frequently used unnecessary force on tissues or caused damage by inappropriate instrument use		Careful handling of tissue, but occasional inadvertent damage		Consistently handled tissues appropriately with minimal damage
Time in motion	Many unnecessary moves		Efficient time and motion, but some unnecessary moves		Clear economy of movement and maximum efficiency

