### Study Procedure

#### Objective 1: Evaluate Students’ Ability to Identify the Correct Subcuticular Suture Method

We will determine the best learning method in a virtual environment among the three main groups. We will compare groups 2, 3, and 4: self-learning, peer-learning, and peer learning with expert feedback. There will be no crossovers. Students will undergo a pretest and a posttest to assess the effect of the intervention on their ability to identify the correct way to perform subcuticular sutures. We will also use the control group to compare our intervention to the regular web-based learning method, in which students learn alone by watching different videos with no artificial errors inserted. We will analyze the students’ scoring of each video with the GRS and Subcuticular Suture Checklist.

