### Study Limitations

The suturing skills of the students before this study are unknown. However, this factor is controlled because all students will be randomized. Only students in their first year of medical school are eligible to participate the study. At this stage of their education, they have not yet received any training in surgical or suturing skills. However, students who are more interested in surgery and with more experience are more likely to participate. This can lead to small effect differences between groups.

A possible limitation is that students may access external material such as other videos on the web or through practicing on their own. However, we will require students to self-report external material they have used or additional practicing they performed. These questions will be asked in the poststudy survey. Because the students will be in their first year of medical school, they will have poor suturing knowledge. Further, the students will only have three days to complete the study and learn a practical skill, which limits the time they can spend on external platforms. Therefore, we do not believe that accessing external material will have a considerable impact on the outcomes.

Learning and practicing for three days at home is not directly comparable to the traditional method in which a single surgeon teaches suturing skills for one to three hours at a university. In this study, we aim to compare different web-based learning methods for a specific skill. Learning on GEN cannot replace the traditional method. Rather, we believe that it represents a potential adjunct and an optimal option in the context of the COVID-19 pandemic.

A vast array of gamification elements have been previously published [19-22]. However, we decided to limit the number of gamification elements used in this study and to focus on our primary objective of evaluating procedural knowledge. Further, limiting the number of gamification elements helps simplify distance learning of an advanced suturing skill for novice learners who are not familiar with that skill.

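### Objective 1 tests pre-post change with paired t tests, which do not compare the arms, and the valid posttest comparison of groups 2-4 leaves the pretest and the surveyed prior experience unused

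*Protocol article*

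**What the plan says.** Under Objective 1 the article sets a between-arm question: "We will determine the best learning method in a virtual environment among the three main groups", meaning groups 2, 3 and 4, with group 1 as an additional comparison. The Statistical Analysis Plan section then gives three analyses.

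- Between arms: "We will perform balanced one-way ANOVA to compare mean GRS and Subcuticular Suture Checklist scores among all four groups".
- Pretest and posttest are kept apart: "distinct analyses of the pretest and the posttest scores will be performed".
- Change: "the mean difference between the pretest and the posttest scores will be compared using paired" t tests, to be used only if the paired differences turn out consistent. That term is not defined.

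For Objective 2: "We will perform balanced one-way ANOVA to compare the performance of students in executing a running subcuticular suture". No covariate is named, and there is no baseline execution score because only a first attempt is recorded.

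Participant Recruitment says that students' "previous experience with suturing will be surveyed, as well as the context of this experience", but this variable appears in no stated analysis. Study Limitations says of prior skill: "However, this factor is controlled because all students will be randomized". The same paragraph expects students with more experience to be more likely to volunteer.

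The pretest differs by arm. In group 1, "each student will individually view eight videos of an expert performing a running subcuticular suture correctly as a pretest". In groups 2-4, six of the eight videos contain errors (Pretest and Posttest section).

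**The concern.** The paired t test is the only stated analysis that uses both measurements, and it does not address the stated question. Run per arm, it shows whether that arm changed. Pooled over arms, it shows whether students as a whole changed. Every arm rates its same eight videos twice, so any arm may change through repetition alone. If one arm's test is significant and another's is not, readers may take that as one method beating the other, which does not follow.

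The posttest ANOVA does compare arms, but it leaves out two measurements that the trial already collects and that could sharpen it in a study of 15 per arm. The pretest ANOVA among groups 2-4 tests a null hypothesis that randomisation already makes true. For Objective 2, a chance imbalance in prior experience would pass unadjusted into the result.

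**Working it through.** **Inputs.** From Sample Size: 15 per group, effect size 0.8, within-group SD 1.45, 80% power, alpha 0.05, 13 per group calculated. The documents do not give the pre-post correlation (rho) or the share of students with prior experience, so both are assumed and shown over a range.

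**1. The plan's own figure.** Power = P[F′(k−1, N−k, λ) > critical F], with λ = N·f². The article does not say what scale the 0.8 is on. Thirteen per group comes back if 0.8 is the SD of the four group means in points (divisor 3) and 1.45 is the within-group SD: f² = (3/4)(0.64)/2.1025 = 0.228, so f = 0.478. With N = 52, λ = 11.9 and power is 80.2%.

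**2. What separate paired tests would show.** If all k arms have the same true gain and each test has power p, the chance that some arms are significant and others not is 1 − p^k − (1−p)^k.

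- p = 0.8: 1 − 0.512 − 0.008 = 48% (three arms); 1 − 0.4096 − 0.0016 = 59% (four arms).
- p = 0.5, where the formula peaks: 75% and 87.5%.

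**3. Power for groups 2-4 (N = 45).** The unadjusted ANOVA has error df 42. ANCOVA with two covariates has error df 40 and λ/(1 − rho²), assuming that prior experience adds nothing beyond the pretest.

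- Scenario A, one arm 0.8 SD from the other two: f = 0.8·√2/3 = 0.377, λ = 6.4.
- Scenario B, f = 0.478 from step 1: λ = 10.3.

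| | Unadjusted | rho 0 | rho 0.3 | rho 0.5 | rho 0.7 |
|---|---|---|---|---|---|
| A | 58% | 58% | 62% | 71% | 87% |
| B | 79.7% | 79.5% | 83% | 90% | 98% |

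**4. Cost of adjusting.** The table ignores chance covariate imbalance. Allowing for it, with c covariates and error df ν, the variance ratio of ANCOVA to ANOVA is (1 − rho²)(1 + c/(ν−1)). For the pretest alone (ν = 41) it is 1.025, 0.93, 0.77 and 0.52 at rho 0, 0.3, 0.5 and 0.7. Break-even is at rho = √(1/41) = 0.16. With a second covariate that explains nothing (ν = 40), break-even moves to √(2/41) = 0.22.

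**5. Chance imbalance in prior experience.** With three independent Binomial(15, q) counts, the probability that two arms differ by 3 or more experienced students is 8%, 26%, 48% and 58% at q = 5%, 10%, 20% and 30%.

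**6. Why group 1 stays out of the ANCOVA.** Suppose that there is no learning effect and that the error-free videos raise both of group 1's scores by 1 SD (assumed). Adjustment removes only rho × 1 SD of that shift, so about (1 − rho) SD remains. Simulation gave a group 1 bias of 0.70, 0.49 and 0.30 SD at rho 0.3, 0.5 and 0.7, with false rejection by the four-arm ANCOVA of 41%, 25% and 16%. The unadjusted four-arm posttest ANOVA rejected about 78% of the time. Neither analysis gives a fair contrast with group 1 on these scores.

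**The case against.** The strongest reply is that the between-arm test is already planned. Groups 2-4 see the same videos in the same order, so comparing their posttest means is a valid randomised comparison, and an unadjusted analysis is legitimate after randomisation. This stands. A reader might infer that the plan has no valid comparison of learning methods, and the documents do not support that.

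A reader might also infer that the investigators mean to rank arms by their separate paired p-values. No such rule is written, and the text does not even say that the paired tests are run within each arm. Step 2 therefore shows a risk of misreading, not a stated decision rule, and its 75% and 87.5% are the worst case.

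It is also fair to say that the gain depends on an unknown correlation and vanishes near zero, so adjustment is not free. Prior experience may be rare: the article says that first-year students have had no suturing training. Chance imbalance is already allowed for in the type I error of a randomised comparison, so leaving the covariate out does not invalidate Objective 2. The documents give no effect of experience on execution, so the harm there cannot be sized.

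Finally, this is a condensed article, and a fuller analysis plan may add covariates. That does not remove the point about the paired tests: the article names the test for change, and the named test does not fit the question it sets.

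**Conclusion.** The point holds in a limited form. The change analysis does not compare arms and depends on an undefined look at the data. The valid comparison of groups 2-4 leaves available baseline information unused.

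The size depends on rho. Under scenario A the power gain is nil at rho 0, about 4 points at 0.3, 13 at 0.5 and 29 at 0.7. At the effect that reproduces the planned sample size, power goes from about 80% to between 79.5% and 98%. These figures assume 15 analysed per arm and a linear pretest-posttest relation common to the three arms.

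For Objective 2 the claim that randomisation controls prior skill is too strong, since it prevents systematic but not chance imbalance. A difference of 3 or more experienced students between two of three arms has a probability of 8% to 58% over the assumed prevalences.

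A tempting extension is a single four-arm ANCOVA for either objective. The documents do not support it: group 1 rates different videos, so its pretest score depends on the arm and is not a common baseline.

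**What to change.** **Objective 1.** For groups 2-4, make the between-arm analysis an ANCOVA of posttest score on group, adjusted for pretest score and prior suturing experience (yes/no). Report adjusted differences with 95% confidence intervals. Give within-arm changes descriptively, without the data-dependent condition, and drop the pretest significance test among groups 2-4. Keep group 1 out of this model and describe its comparison separately, stating that its tests use different videos.

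**Objective 2.** Add prior suturing experience as a covariate to the ANOVA in all arms. Use the pretest score, if at all, only in an analysis of groups 2-4, as a proxy whose correlation with execution is unknown.

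**Study Limitations.** Replace the sentence saying that prior skill is controlled with one saying that randomisation prevents systematic but not chance imbalance, and that the analysis adjusts for surveyed experience.

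**Cost.** This is a change of wording. Both covariates are already to be collected, and the Abstract reports that no participant has been recruited. The Objective 1 model uses two residual degrees of freedom and loses a little precision if rho is below about 0.16 (0.22 if prior experience explains nothing).

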### Sample Size

The experiment is designed so that each of the four groups will have the same sample size. We calculated the sample size based on our primary objective considering a balanced one-way analysis of variance (ANOVA) model. We used the GRS for the calculation.

In the study by Denadai et al [8], subcuticular sutures were assessed using the GRS among three intervention groups. The difference between the lowest mean and the highest mean was 12.25. In that study, we approximated the mean standard deviation within groups to be 1.45. We chose to set the effect size at 0.8 because we do not know the overall standard deviation for all participants. We set the power to 80% and the significance level to 0.05.

Using RStudio, we obtained a sample size of 13 participants per group and a total sample size of 52. We will include 15 participants in each group (total N=60) to have sufficient statistical power. We will invite the whole cohort of first-year medical students (n=300) and enroll the first 60 students who reply favorably.

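### The aim is to find the best of groups 2, 3 and 4, but the Objective 1 test is a four-group ANOVA including control, on two scales with neither named primary

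*Protocol article*

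**What the plan says.** All references are to the protocol article.

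- **Aim.** Under Objective 1: "We will determine the best learning method in a virtual environment among the three main groups". The next sentence names the arms: "We will compare groups 2, 3, and 4: self-learning, peer-learning, and peer learning with expert feedback". Objective 2 repeats the aim for execution of the suture.
- **Role of control.** It is an additional comparator: "We will also use the control group to compare our intervention to the regular web-based learning method".
- **Between-group test for Objective 1** (Statistical Analysis Plan): "We will perform balanced one-way ANOVA to compare mean GRS and Subcuticular Suture Checklist scores among all four groups". On timing: "First, distinct analyses of the pretest and the posttest scores will be performed".
- **Other tests.** Paired t tests of pretest against posttest follow for Objective 1. Objective 2 gets a one-way ANOVA on the same two scales, without saying which arms enter it.
- **Threshold.** "Statistical hypothesis testing will be performed with an alpha threshold of .05". No split between scales and no order is given.
- **Primary scale.** The Abstract uses both scales for the primary outcome. The Sample Size section singles out one: "We used the GRS for the calculation".

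**The concern.** Naming a best method among three needs comparisons within those three. A four-group F test addresses a different hypothesis, that four means including control are all equal. If it is significant, it does not say which arm differs, and the cause may be control alone. The paired t tests do not help, because they look at change within participants and not at differences between arms.

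The design makes a difference confined to control plausible. Group 1 rates eight videos of a correctly performed suture (Group 1: Control Group). Groups 2 to 4 rate eight videos of which six contain errors (Pretest and Posttest). Control's scores therefore rest on different material and could differ even if everyone learned equally well.

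The second part concerns the scales. Each is tested at .05 and neither is named primary, so the text does not say what happens if only one is significant. The headline conclusion on learning methods is at stake.

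**Working it through.** **Inputs.** Sample Size section: four equal groups, 15 planned per group, 13 per group calculated, effect size 0.8, within-group SD 1.45, alpha .05, power 80%. Assumed here, because the article does not give them: the size of a control-only difference, and the correlation between the GRS and the checklist.

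**1. The plan's own sample size.** Power of a balanced one-way ANOVA comes from the noncentral F with λ = k·n·f², k − 1 and k(n − 1) degrees of freedom.
- Reading 0.8 as Cohen's f with k = 4 gives 6 per group, not 13. At 13 per group the power would be 99.9%.
- Thirteen per group corresponds to f of about 0.48: λ = 4 × 13 × 0.48² = 11.98, power 80.5%. With 12 per group it is 76.6%.
- That f arises if 0.8 is taken as the between-group SD and 1.45 as the within-group SD: √(0.64 × (3/4) / 2.1025) = 0.478.

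The failure of 0.8 to give 13 is a separate matter. Here f = 0.48 serves only to cost the fix.

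**2. What the four-group F does when only control differs.** Let control differ by d SD from three identical arms. The grand mean is shifted by d/4, so f² = [(3d/4)² + 3(d/4)²]/4 = 3d²/16, and λ = 60 × 3d²/16 = 11.25d². The critical F on 3 and 56 degrees of freedom is 2.77.

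| d (SD) | f | λ | Probability of rejecting |
|---|---|---|---|
| 1.0 | 0.433 | 11.25 | 78% |
| 1.5 | 0.650 | 25.31 | 99% |

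Groups 2, 3 and 4 are exactly equal in both rows.

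**3. Two posttest F tests, each at .05, with no true difference.** If the scales were independent, 1 − 0.95² = 9.75%. With correlated scales (simulation, 40,000 runs, 4 × 15):

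| Assumed scale correlation | At least one significant |
|---|---|
| 0.3 | 9.5% |
| 0.5 | 9.0% |
| 0.7 | 8.4% |
| 0.8 | 7.8% |
| 0.9 | 7.1% |

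Only perfect correlation brings this back to 5%.

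**4. Does a three-group gate followed by pairwise tests hold 5%?** Take an F test of groups 2 to 4 at .05, then the three contrasts each at .05 if it is significant. If all three means are equal, an error needs the gate to reject, which has probability 5%. If exactly two are equal, only one true null contrast remains, tested at 5%. Simulation with 15 per arm gives about 5% in both cases.

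**5. Power of the gate at f = 0.48 with 15 per arm.**
- Three groups: λ = 3 × 15 × 0.2304 = 10.37, power 80%.
- Four groups: λ = 4 × 15 × 0.2304 = 13.82, power 87%.

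**The case against.** The strongest reply is that this is a condensed article. Post hoc comparisons and multiplicity rules often sit in a fuller analysis plan, which may add contrasts among groups 2 to 4. The text also says that descriptive analyses come first to settle the appropriate tests, and it promises 95% confidence intervals for each analysis. Control was included deliberately, since both objectives say it will also be compared.

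Part of this stands. A reader might infer that the trial cannot identify a best method at all. The article does not support that, because silence on contrasts here does not exclude them elsewhere. But the point does not rest on silence: the article does state the between-group test for the primary objective, and that test does not match the question stated two sections earlier. The descriptive step concerns distributions and transformation, not which arms are compared.

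Two further inferences should be resisted.
- A reader might take the alpha sentence as a promise of 5% overall that the plan then breaks. It sets a threshold for testing; no family-wise rate is promised and no rule for declaring success is stated.
- A reader might put the inflation at several times 5% by counting between-group tests of change or unadjusted pairwise tests. The article plans neither. The supportable figure covers the two posttest F tests only.

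For Objective 2 the arms in the ANOVA are not stated, so the charge that control is pooled in applies to Objective 1 alone.

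**Conclusion.** The point holds as a mismatch between a stated aim and a stated test. For Objective 1, a significant four-group F need not say anything about groups 2 to 4. The 78% and 99% figures assume control-only differences of 1.0 and 1.5 SD, normal scores and 15 per arm. The article does not give the true size of such a difference, but the different video material makes one plausible.

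The lack of a primary scale is the smaller part. It raises the chance of at least one false-positive posttest F to about 7% to 9.5%, for an assumed scale correlation between 0.9 and 0.3. The higher end of that correlation range is credible, because the same student completes both scales on the same videos.

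This should be corrected. Otherwise the planned primary test could be significant while leaving the stated question open.

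**What to change.** In the Statistical Analysis Plan section, for Objective 1:

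1. Name the GRS, the scale used for sizing, as the primary score.
2. Make the primary test a one-way ANOVA of groups 2, 3 and 4 only, at .05.
3. If it is significant, test the three pairwise contrasts each at .05 and report the differences with 95% confidence intervals. With exactly three groups, no further adjustment is needed.
4. Treat the checklist and the contrasts with control as secondary. Alternatively, pass the full .05 to them, in a stated order, only if all three GRS contrasts are significant. The gate must be that strict. If the three-group F alone opened the checklist, simulation with one arm shifted by 2 SD on the GRS and no checklist effect gives a family-wise error of about 8% to 10%.
5. State which arms enter the Objective 2 ANOVA.

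The change is to wording only, and the Abstract reports that recruitment has not begun. There are costs. The checklist and control contrasts will usually be supportive only. At f of about 0.48 with 15 per arm, the primary test has about 80% power instead of 87%. A single pairwise contrast at .05, before the gate, has about 56% power for a difference of 0.8 SD and 75% for 1.0 SD, so a clear ranking of the three methods needs large differences.
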